# INFLATE: a protocol for a randomised controlled trial comparing nasal balloon autoinflation to no nasal balloon autoinflation for otitis media with effusion in Aboriginal and Torres Strait Islander children

**DOI:** 10.1186/s13063-022-06145-8

**Published:** 2022-04-14

**Keywords:** Otitis media, Otitis media with effusion, Aboriginal and Torres Strait Islander, Indigenous, Children, Nasal autoinflation, Randomised controlled trial, Ear disease, Otolaryngology

## Abstract

**Background:**

Otitis media with effusion (OME) is common and occurs at disproportionately higher rates among Indigenous children. Left untreated, OME can negatively affect language, development, learning, and health and wellbeing throughout the life-course. Currently, OME care includes observation for 3 months followed by consideration of surgical ventilation tube insertion. The use of a non-invasive, low-cost nasal balloon autoinflation device has been found beneficial in other populations but has not been investigated among Aboriginal and Torres Strait Islander children.

**Methods/design:**

This multi-centre, open-label, randomised controlled trial will determine the effectiveness of nasal balloon autoinflation compared to no nasal balloon autoinflation, for the treatment of OME among Aboriginal and Torres Strait Islander children in Australia. Children aged 3–16 years with unilateral or bilateral OME are being recruited from Aboriginal Health Services and the community. The primary outcome is the proportion of children showing tympanometric improvement of OME at 1 month. Improvement is defined as a change from bilateral type B tympanograms to at least one type A or C1 tympanogram, or from unilateral type B tympanogram to type A or C1 tympanogram in the index ear, without deterioration (type A or C1 to type C2, C3, or B tympanogram) in the contralateral ear. A sample size of 340 children (170 in each group) at 1 month will detect an absolute difference of 15% between groups with 80% power at 5% significance. Anticipating a 15% loss to follow-up, 400 children will be randomised. The primary analysis will be by intention to treat. Secondary outcomes include tympanometric changes at 3 and 6 months, hearing at 3 months, ear health-related quality of life (OMQ-14), and cost-effectiveness. A process evaluation including perspectives of parents or carers, health care providers, and researchers on trial implementation will also be undertaken.

**Discussion:**

INFLATE will answer the important clinical question of whether nasal balloon autoinflation is an effective and acceptable treatment for Aboriginal and Torres Strait Islander children with OME. INFLATE will help fill the evidence gap for safe, low-cost, accessible OME therapies.

**Trial registration:**

Australia New Zealand Clinical Trials Registry ACTRN12617001652369. Registered on 22 December 2017. The Australia New Zealand Clinical Trials Registry is a primary registry of the WHO ICTRP network and includes all items from the WHO Trial Registration data set. Retrospective registration.

**Supplementary Information:**

The online version contains supplementary material available at 10.1186/s13063-022-06145-8.

## Introduction

### Background

Otitis media with effusion (OME) is a common health condition among Aboriginal and Torres Strait Islander children in Australia with limited treatment options. This clinical trial investigates the effectiveness of nasal balloon autoinflation, a relatively inexpensive and readily available treatment for OME.

#### Diagnosis and incidence of otitis media with effusion

Otitis media with effusion, one of several inflammatory middle ear diseases collectively known as otitis media (OM), is characterised by accumulated fluid (effusion) and reduced air pressure in the middle ear space [1]. It is diagnosed by otoscopy and tympanometry [2].

**Table Taba:** 

**Tympanometry:** Best practice guidelines [2, 3] recommend pneumatic otoscopy and tympanometry for the diagnosis of OME. Tympanometry is a non-invasive test measuring tympanic membrane movement and middle ear air pressure — a proxy for determining the presence of middle ear effusion — and is depicted in graphical form (tympanogram). Tympanograms are classified as type A, B, C1, C2, or C3. Peaked type A and C1 tympanograms indicate the absence of effusion consistent with normal middle ears. A flat type B trace is diagnostic of middle ear effusion in the absence of pain and/or a bulging or perforated tympanic membrane. Type C2 and C3 peaked traces are characterised by significant negative middle ear pressure and are considered equivocal and cannot be used to either diagnose or exclude OME [4, 5].	

Acute otitis media (AOM) is a frequent reason for children to attend general practice and often results in the prescription of antibiotics [6, 7]. Resolution of AOM is often followed by a period of residual middle ear fluid, or OME. The prevalence of OME in Aboriginal and Torres Strait Islander children is disproportionately high, ranging from 10 to 30% [8, 9]. The risk factors are multifactorial including household crowding and poor functionality [10], exposure to tobacco smoke, food insecurity, child care attendance, older siblings, upper respiratory tract infection, family history, lack of breastfeeding [8], and socioeconomic disadvantage and other adverse social determinants of health arising as a consequence of ongoing colonisation [11, 12]. The duration and severity of disease, and the incidence of complications, are also higher among Aboriginal and Torres Strait Islander people, particularly in remote and rural regions of Australia [13, 14].

#### Prognosis and treatment of otitis media with effusion

In the absence of medical intervention, 30% of OME cases in children resolve within the first month of diagnosis, and 90% within 3 months of diagnosis, as determined by international longitudinal research [15]. Although most cases resolve spontaneously by 3 months, recurrent episodes and persistent OME can result in impaired hearing and delay in language development with a negative impact on education and wellbeing [16–18]. All forms of OM, including OME, are associated with hearing loss, increasing in severity with more severe forms of OM [19].

Treatment options for episodic, unilateral, or persistent OME are limited. Treatment with antibiotics is of minimal benefit, and not without risk, for improving resolution of OME, hearing, or reducing tympanostomy tube insertion [20], while nasal decongestants and steroids are of no benefit [21, 22]. Guidelines for OM in Aboriginal and Torres Strait Islander children recommend that children with persistent bilateral OME for 3 months are referred to an audiologist for a diagnostic hearing assessment and to an Ear Nose and Throat surgeon (ENT) to consider insertion of tympanostomy tube(s) to re-establish normal middle ear pressure. This enables clearing of the middle ear effusion and aeration of the middle ear space [21], thereby reducing the risk of longer term hearing loss and other complications. However, there are temporal and financial costs and health risks associated with this approach. The deferral of surgical tympanostomy tube insertion to at least 3 months after initial diagnosis means no active treatment and a potential decline in hearing in children with persistent OME, during this period. Additionally, access to surgery is extremely limited for many Aboriginal and Torres Strait Islander children with OM living in rural and remote areas where surgical wait lists can be years [23]. Furthermore, although unilateral OME is increasingly being recognised as contributing to adverse outcomes including spacial processing disorder [24], guideline-recommended treatment approaches for unilateral disease based on high-quality intervention studies are lacking.

Surgical tympanostomy tube insertion (with or without adenoidectomy) is costly [7, 25]. Surgical intervention is also limited in its long-term effectiveness [26] and has been shown to result in a 26–37% incidence of post-tympanostomy infection [27, 28]. There is a need for an immediate, low-risk, cost-effective, and easy-to-use alternative treatment for both bilateral and unilateral OM. Nasal balloon autoinflation may be useful immediately upon diagnosis of bilateral or unilateral OME.

#### Nasal balloon autoinflation

Nasal balloon autoinflation is designed to introduce air into the middle ear and facilitate fluid drainage. It can be performed by a person with OME, in any location, potentially offering a possible low-cost, low-risk, readily accessible, and easy-to-use alternative to ventilation tube surgery [29].

The effects of nasal balloon autoinflation on OME, measured using tympanometry and audiometry, were examined in a 2013 Cochrane review consisting of a pooled analysis of 8 small trials (7/8 studies with ≤100 participants) [30]. No statistically significant difference was shown for tympanometry changes; however, a composite measure of tympanometric or audiometric improvement showed nasal balloon autoinflation for OME was effective at more than 1 month, compared to no nasal balloon autoinflation (relative risk increase = 1.74; 95% confidence interval 1.22 to 2.50). Treatment adherence varied from 43 to 98%. There was no significant difference in adverse events between nasal balloon autoinflation and no nasal balloon autoinflation, with one study documenting ear pain with balloon autoinflation. The authors interpreted the findings as ‘favourable’ but noted that the included studies were small, and recommended further research in primary care. A subsequent study published in 2015 of 320 children (4–11 years) with unilateral and bilateral OME showed tympanometric resolution at 3 months (adjusted relative risk = 1.37, 95% confidence interval 1.03 to 1.83) in a nasal balloon autoinflation group versus no nasal balloon autoinflation group [31]. The study also reported improved ear health-related quality of life and good adherence to treatment (80% at 3 months). Another study of 45 children demonstrated improvement in hearing thresholds after 1 month (difference = dB. 95% CI) and concluded the device could be useful while children were on waiting lists for surgical treatment [32]. Although Aboriginal and Torres Strait Islander children are at increased risk of OM complications, no studies of nasal balloon autoinflation have been undertaken in this population.

## Methods/design

INFLATE is a pragmatic, multi-centre, two-arm, open-label, parallel design, superiority, randomised controlled trial comparing nasal balloon autoinflation to no nasal balloon autoinflation for the treatment of OME among Aboriginal and Torres Strait Islander children.

### Aim

The INFLATE trial aims to investigate whether, among Aboriginal and Torres Strait Islander children aged 3 to 16 years with unilateral or bilateral OME, nasal balloon autoinflation increases the resolution of middle ear effusion compared with no nasal balloon autoinflation based on tympanometry.

*Null hypothesis (H0)*: The proportion of children with tympanometric improvement at 1 month from baseline will be equal in the nasal autoinflation and no nasal autoinflation (usual care) groups.

*Alternative hypothesis (H1)*: The proportion of children with tympanometric improvement at 1 month from baseline will be less in the nasal autoinflation treatment group compared to the usual care treatment group.

### Primary objective

To determine whether, among Aboriginal and Torres Strait Islander children aged 3 to 16 years with OME, nasal balloon autoinflation compared to no nasal balloon autoinflation improves unilateral and bilateral OME determined by tympanometric findings at 1 month from baseline.

### Secondary objectives

Determine whether nasal balloon autoinflation compared to no nasal balloon autoinflation
Improves unilateral and bilateral OME determined by tympanometric findings at 3 and 6 months from baselineReduces hearing loss at 3 months from baselineImproves ear-related health and quality of life at 3 and 6 months from baselineDetermine
Adverse events up to 1, 3, and 6 months from baselineParent/carer/child reported adherence to nasal balloon autoinflationCost-effectiveness of nasal balloon autoinflation for the management of OMEParent/carer, health care provider, Aboriginal Health Service Research Officer, and community reference group views regarding nasal balloon autoinflation acceptability and use, OME and its management, research in Aboriginal Health Services, and the implementation and receipt of the trial

### Setting

The trial is being conducted in urban and regional Aboriginal and Torres Strait Islander primary health care services across Australia (New South Wales, Queensland, the Australian Capital Territory, and Victoria). The services include Aboriginal community-controlled health services governed by local Aboriginal communities and one state government-run Aboriginal and Torres Strait Islander primary health care facility. The Aboriginal Health Service staff are multidisciplinary, including dedicated Aboriginal Health Workers and often contracted services providing ear and hearing health care. At the time of initiation of INFLATE, some services were already participating in the WATCH trial, a clinical trial of the management of acute otitis media [33]. The two trials have shared governance, implementation of recruitment, and staff.

### Governance, mentorship, and training

A Steering Committee, Operational Management Group, a Data Safety Monitoring Board (DSMB), and other working groups consisting of chief investigators (CIs), associate investigators (AIs), and Aboriginal Health Service research staff meet regularly to ensure the protocol is implemented correctly, recruitment is monitored, issues are addressed as they arise, and to develop, refine, implement, and document trial materials and processes. All Aboriginal Health Services are encouraged to establish Aboriginal and Torres Strait Islander community reference groups or equivalent structures. Consultation and communication with and between each service and their community are conducted regularly to review local implementation of the trial, maintain community engagement, and regularly disseminate trial findings to the community. Management of the trial between investigators and Aboriginal Health Services is a non-hierarchical partnership, recognising the different expertise, experiences, and knowledge necessary to successfully conduct research in Aboriginal and Torres Strait Islander primary health care and facilitate knowledge transfer.

Aboriginal and/or Torres Strait Islander researchers and local community reference groups provide input into and feedback from trial implementation in the Aboriginal and Torres Strait Islander primary health care setting and assist other team members to ensure all stakeholders remain respectful towards and learn from participating Aboriginal and Torres Strait Islander communities. Community reference group members are remunerated for their time during 6–12 monthly community reference group meetings while health services are remunerated for patient recruitment and follow-up in recognition of General Practitioner (GP) time.

Service staff and local communities are building research and ear health-related skills, knowledge, and experience. Service staff are regularly trained in research practices and the use of pneumatic otoscopy and tympanometry to detect middle ear effusion, during service initiation and monitoring visits, at biannual face-to-face investigator meetings, and via regular trial emails and newsletters. Concurrently, Western Sydney University (WSU) staff are building their understanding of best practice in the implementation of clinical trials in the Aboriginal Health Service setting.

### Study population/eligibility criteria

Aboriginal or Torres Strait Islander children, attending urban or regional Aboriginal Health Services, aged 3–16 years with unilateral or bilateral type B tympanograms are eligible for inclusion. Tympanometry is conducted by a trained research officer (RO), and eligibility, including trace type, is confirmed by the treating General Practitioner (GP). Exclusion criteria include clinical confirmation of a current acute upper respiratory infection, acute otitis media, perforated tympanic membrane, or ventilation tube in situ; ear surgery booked within 1 month of diagnosis; self-reported latex allergy, recent nosebleed (at least 1 nosebleed in last 3 weeks or > 1 nosebleeds in last 6 months); self-reported or documented history of an at-risk condition (e.g., immunosuppression); previous participation in the trial; or self-reported inability to use the autoinflation device (demonstrated by the inability to blow nose).

### Recruitment strategies

Recruitment strategies include a review of existing health service clinical databases for patients with a history of ear disease, opportunistic screening of children visiting health services, school ear screenings and community health promotion events, advertising via promotional posters and flyers in all health service waiting rooms and at health promotion events, and providing regular trial updates to health service staff and community reference groups via meetings, newspaper articles, and periodic emails and newsletters.

### Screening/enrolment

Aboriginal Health Services are funded to recruit research officers (ROs) who, with GPs and other health care providers, identify potential participants by reviewing existing health service clinical databases and medical records for children with past and/or current OM. Treating clinicians or their delegate then contact a child’s parent/carer via phone or mail to inform them about the trial and assess their interest in participating. Children of interested parent/carers are invited to attend the health service for formal screening and confirmation of eligibility. Research officers, GPs, and other health care providers also opportunistically screen all children visiting Aboriginal Health Services regardless of the reason for attendance, and at school ear screenings and community health promotion events and, if found eligible, formal screening is offered to confirm eligibility. Children are considered enrolled where eligibility is confirmed by a GP and written informed consent to participate is obtained. Randomisation and baseline assessments are conducted immediately following enrolment (day 0).

### Treatment groups

The intervention group uses a nasal balloon autoinflation device, Otovent® [34], in both nostrils three times daily from baseline (day 0) for up to 3 months. Participants are instructed to temporarily cease autoinflation treatment while symptomatic for no more than 5 consecutive days in the event of an upper respiratory tract infection to minimise the potential for ear pain during autoinflation. Participants cease autoinflation at 1 month if they have bilateral type A, C1, C2, or C3 tympanograms. Those with a type B tympanogram in at least one ear are asked to continue autoinflation for a further 2 months. At 3 months, participants are advised to cease autoinflation irrespective of tympanogram results.

The control group is managed according to Australian treatment guidelines (usual care) and regular follow-up with ROs, without autoinflation. General Practitioners decide usual care taking into consideration a participant’s risk of more severe forms of OM.

Antibiotics, steroids, antihistamines, decongestants, and alternative therapies are not recommended use during trial participation. All children in the intervention and control groups undergo a hearing assessment by an audiologist at either the Aboriginal Health Service or an audiology service provider. Any participants with bilateral OME or hearing impairment at 3 months are reviewed by a GP for appropriate management, including referral for ENT assessment.

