### Randomisation

Participants are randomised to the intervention or control group by the RO using an automated Interactive Voice Response System (IVRS) located at the National Health and Medical Research Council Clinical Trials Centre (NHMRC CTC), Sydney, Australia. The IVRS, accessible by telephone, uses a computer-generated randomisation sequence, enabling immediate 1:1 allocation to unblinded treatment groups. Participants and health service and WSU staff are not blinded to treatment allocation due to the nature of the intervention. Randomisation is stratified using permuted block design (block size 4), based on participating site, child age (3 to 5 years versus 6 to 16 years), and whether unilateral or bilateral OME at presentation. These strata were determined a priori given their potential association with effectiveness.

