### Sample size and power

It is estimated that a sample size of 340 children (170 in each treatment group) will detect an absolute difference of 15% between groups (relative difference relative risk = 1.43) in OME resolution rates at 1 month, with 80% power and a 5% significance level. The 15% difference represents a difference between an estimated 35% resolution in the control group and 50% resolution in the treatment group based on a similar trial [36]. This 15% absolute difference reduces the 65% non-resolution by approximately a quarter, which is clinically relevant. Assuming a 15% loss to follow-up, 400 children will need to be randomised. This sample size will also detect an effect size of 0.3 (assuming a standardised standard deviation = 1) for continuous secondary outcomes, such as OMQ-14 scores.

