#### Secondary outcomes

The secondary outcomes are:
i)Proportion of children showing tympanometric improvement at 3 and 6 months from baseline (OME improved by child)ii)Proportion of ears showing tympanometric resolution of OME at 1, 3, and 6 months from baselineiii)Proportion of children showing tympanometric improvement at 1, 3, and 6 months from baseline (OME improved by child — unilateral and bilateral subgroups)iv)Proportion of tympanometric deterioration from a type A or C1 tympanogram to C2, C3, or B tympanogram in non-index ears at 1, 3, and 6 months from baseline (new OME by ear — unilateral subgroup)v)3-frequency average hearing levels (pure tone threshold audiometry) at 3 months from baselinevi)Ear-related health and quality of life score (using OMQ-14 quality of life questionnaire) at day 0 and months 3 and 6vii)Adverse events up to 6 months from baselineviii)Adherence to autoinflation from day 0 to month 1 (using paper adherence diary)ix)Medical and non-medical costs of OME and its treatmentx)Qualitative exploration of parent/carer and health care provider, AMS Research Officer and AMS reference group perspectives of otitis media, research processes and the research experience including the experience of using nasal balloon autoinflation

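### The reason given for leaving health service staff unblinded does not cover an audiologist who only tests hearing, and the protocol makes no provision for masking that test

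*Protocol article*

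**What the plan says.** All references are to the protocol article.

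- **Methods/design** describes a "pragmatic, multi-centre, two-arm, open-label, parallel design, superiority, randomised controlled trial".
- **Randomisation** describes a telephone system "enabling immediate 1:1 allocation to unblinded treatment groups" and then states: "Participants and health service and WSU staff are not blinded to treatment allocation due to the nature of the intervention". No other reason for the lack of blinding is given.
- **Treatment groups** has children in both arms "undergo a hearing assessment by an audiologist at either the Aboriginal Health Service or an audiology service provider".
- **Secondary outcomes**, item (v), is "3-frequency average hearing levels (pure tone threshold audiometry) at 3 months" after baseline. Reducing hearing loss at 3 months is also listed under Secondary objectives.
- **Setting** says that the services' staff include "often contracted services providing ear and hearing health care".

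No section describes a masked assessor for any outcome, and none says whether audiologists, on site or outside, are told the allocation.

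**The concern.** The stated reason for not blinding is sound for the child, the family and the research officer, who randomises the child, telephones about technique and adherence, and runs follow-up. It does not carry over to a person whose only described task is to test hearing. An open-label design rules out masking of participants, but it does not by itself rule out masking of an assessor.

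Pure tone threshold testing depends on the child's responses and on the tester's reading of them. The article gives no test procedure, so this is a general description of the method, not something taken from the text. Eligible children are as young as 3, and the room for judgement is plausibly largest at that age. A tester who knows the arm could shift measured thresholds in either direction without intending to. The generalised linear models, multiple imputation and per-protocol analyses planned for secondary outcomes cannot remove such a shift afterwards.

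At stake is one secondary outcome, though one close to the trial's rationale: the Background ties OME to impaired hearing, language and education.

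**Working it through.** **1. The plan's own figures.** Under Sample size and power, "a sample size of 340 children (170 in each treatment group) will detect an absolute difference of 15% between groups" "with 80% power and a 5% significance level", with 35% resolution in controls and 50% with treatment. Using the two-proportion formula, two-sided, without continuity correction:

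n = [1.96 × √(2 × 0.425 × 0.575) + 0.842 × √(0.35 × 0.65 + 0.50 × 0.50)]² / 0.15² ≈ 169.3, rounded up to 170 per arm, or 340 in total.

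Allowing for 15% loss, 340 / 0.85 = 400. Both figures reproduce.

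The same section says that this sample will detect 0.3 SD on continuous secondary outcomes; hearing level is one of these. With 170 per arm the standard error of a mean difference is √(2/170) = 0.1085 SD, so 0.3 SD is 2.77 standard errors and power is 79%. That agrees with the text.

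**2. Who is covered by the blinding statement.**

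| Audiologist | Status as written |
|---|---|
| On the health service staff | Unblinded, for a reason that does not fit the task |
| Contracted by the service | Not stated |
| At an outside audiology provider | Not stated |

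**3. What a tester-related shift would do.** The article gives no size for such a bias and no SD for hearing level, so the shift b (in SD units) is an assumption shown over a range. With no true effect, the probability of a two-sided 5% result is P(|Z + b × √(n/2)| > 1.96), with n per arm.

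| Assumed shift b | 170 per arm (√85 = 9.22) | 70 per arm (√35 = 5.92) |
|---|---|---|
| 0 | 5% | 5% |
| 0.1 SD | 15.2% | 9.1% |
| 0.2 SD | 45.4% | 21.9% |

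At 170 per arm, shifts of 0.05 and 0.15 SD give 7.5% and 28.2%. The figure of 70 per arm is a rounding of 137 / 2 = 68.5, from the 137 children randomised by January 2022 (Trial status). If the SD were 10 dB, also an assumption, 0.1 and 0.2 SD would be 1 and 2 dB.

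**4. The opposite direction.** With a true effect of 0.3 SD, 170 per arm and a shift against the device, power falls from 79% to 45.4% (shift 0.1 SD) or 15.0% (shift 0.2 SD).

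**5. Effect of masking on the design figures.** None: 340, 400 and 0.3 SD all stand.

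**The case against.** The case against is substantial, and several parts of it stand.

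- **A separate tester is not established.** A reader might infer that the audiologist always stands outside the treating team. The text allows testing at the health service and gives no proportions. What can be said is that no section gives audiologists a part in delivering or supporting the device.
- **Silence in a condensed article.** A reader might infer that outside audiologists know the arm. The article does not say so, and the full protocol or an audiology procedure may deal with it. Only the on-site staff case rests on stated text, and only if that audiologist counts as health service staff.
- **Masking is not free.** Source data sit in medical records open to authorised health service staff (Data management), and the hearing result must still reach the GP who reviews the child at 3 months. A request without the arm therefore needs some care to set up.
- **The remedy is partial.** Parents and children stay unblinded, and the child's own responses are part of the measurement. Recruitment began in December 2017, so a change would mix earlier unmasked tests with later masked ones.
- **The arithmetic shows sensitivity, not evidence.** Any continuous outcome with the same assumed shift would give the same percentages. The 170 per arm was set for the 1-month primary outcome, not for usable 3-month audiometry.

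These points limit the claim but do not remove it. The blanket statement is positive text rather than an omission, and its one reason does not reach a person who only tests hearing.

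**Conclusion.** The point holds as a gap in protection of one secondary outcome. As written, an audiologist on the health service staff is unblinded for a reason that does not apply to the task, and the position of contracted and outside audiologists is left open. Tester expectation could therefore bias the 3-month hearing comparison in either direction.

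The size is unknown. The increase in false positives from 5% to about 15% or 45% (170 per arm), or to about 9% or 22% (70 per arm), depends wholly on the assumed shift of 0.1 or 0.2 SD and on that many children having usable audiometry.

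A reader might go further and conclude that the hearing result is biased, or that masking the tester would make it unbiased. The documents support neither: no bias is shown, and the unblinded child's responses would remain. The primary tympanometric outcome is measured differently and is a separate matter. An inexpensive amendment is worthwhile; nothing here calls the sample size or the main comparison into question.

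**What to change.** Amend Treatment groups and Randomisation, for hearing tests still to be done, as follows:

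- State that the audiologist, on site or outside, is not told the allocation where this is feasible, and confine the stated reason for not blinding to those whom it fits.
- Use an audiology request that does not show the arm but can still be linked to the child's care.
- Ask families beforehand not to mention the allocation.
- Have the audiologist record after the test whether the arm became known.
- Report hearing results by masked and unmasked test as a sensitivity analysis. Splitting by whether the masked procedure was in force on the test date is the cleaner version. Whether masking actually broke may itself depend on arm, so that split should be read with caution.

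The cost is a protocol amendment, a neutral form, a short instruction to families and one extra data item, with no added staff or tests. Masking will sometimes fail, through the child, the parent or shared medical records. Tests already done stay unmasked, and bias from the child's own knowledge of treatment is not removed. If the full protocol already masks audiologists, a sentence saying so is enough.
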